**Summary of revision of the protocol**

|  | Version | Date of version | Drafter/  reviser | Contents of revision |
| --- | --- | --- | --- | --- |
| 1 | 1.4 | Jun. 9, 2017 | [name], [name], [name] | (This was the first version approved by the ethics committee before recruiting patients). |
| 2 | 1.5 | Jul. 2,  2017 | [name], [name], [name] | 1) Expanded the estimated sample size to 2000 in nine study sites (clause 4.2).  2) Clarified that “this trial will be conducted in 9 obstetric-led maternity units in China” (clause 4.3). |

**1. Background**

The recommendations to particularly restrict oral intake in laboring women came from Mendelson’s work in the 1940s, which reported an increased risk of aspiration of gastric contents in the event that general anesthesia was required [1]. However, from a physiological perspective, it is crucial to supply sufficient energy and hydration for women during labor, which is similar to performing moderate, continuous aerobic exercise [2]. Starvation decreases hepatic glycogen stores, induces a state of insulin resistance [3, 4], and impairs cardiovascular function [5]. Adequate maternal calorie supply during labor is fundamental to ensure effective uterine contractions [6]. Energy depletion during labor can stimulate alterations in the acid–base balance of the myometrium, provoke a reduction in contractility and prolong labor [7], as well as increase the probability of a cesarean delivery [6]. With the development of obstetric anesthesia, pulmonary aspiration during general anesthesia for cesarean delivery has declined dramatically in recent years [8]. The American Society of Anesthesiologists (ASA) and the American College of Obstetricians and Gynecologists (ACOG) prudently recommended that “the oral intake of modest amounts of clear liquids (e.g., water, black coffee, and sports drinks) may be allowed for uncomplicated laboring patients”; however, “solid foods should be avoided in laboring patients” [9, 10]. For more than 15 years, the debate regarding traditional oral intake restriction regimens during labor has never been ceased.

Labor has been described as a prolonged exercise [11]. As there is still a general lack of knowledge concerning the energy expenditure during labor, studies focusing on this field often reference recommendations in sports medicine. According to the advice of the American College of Sports Medicine, athletes who are undertaking intense, moderate and intermittent exercise should ingest carbohydrate solutions; this can not only enhance the capacity of performance but also decelerate the occurrence of exhaustion [12]. Oral rehydration solutions with carbohydrate polymers have been designed to reduce the negative effects of fasting [13]. Maltodextrin carbohydrate polymer allows for the absorption of sufficient glucose to stimulate insulin secretion to restore glycogen stores, similar to the consumption of a meal [14]. Epidural analgesia is frequently used during labor to relieve pain intensity and attenuates stress response [15]. According to the ASA and ACOG guidelines, the Chinese Society of Anesthesiologists Task Force on Obstetric Anesthesia encourages parturients to ingest an energy-dense, low residue beverage during epidural labor analgesia [16]. At present, clear liquids (mostly commercial sports drinks) are allowed in parturients with epidural labor analgesia in some Chinese hospitals [17]. However, these liquid beverages only provide limited amount carbohydrate. Furthermore, available studies have compared the effectiveness of carbohydrate drink to either fasted parturients or a carbohydrate-free placebo of water or flavored water [18]. None of these studies included common, commercial sports drinks with lower carbohydrate content and compared their effects against beverages with a higher carbohydrate content. We speculated that, for women in labor with epidural analgesia, the intake of carbohydrate-rich drink might improve mothers’ performance and reduce cesarean delivery.

**2. Purposes of the study**

To observe the impact of carbohydrate-rich drink on the incidence of cesarean delivery in laboring women with epidural analgesia.

**3. Participants**

***3.1 Inclusion Criteria***

3.1.1 Primipara with a single cephalic pregnancy beyond 37 weeks.

3.1.2 Admitted to the delivery ward for vaginal birth and request epidural labor analgesia.

***3.2 Exclusion Criteria***

Patients who meet any of the following criteria will be excluded.

3.2.1 Age <18 or >34 years.

3.2.2 Comorbid diabetes mellitus or gestational diabetes mellitus.

3.2.3 Suspected fetal abnormalities by prenatal ultrasonography.

3.2.4 Presence of contraindications to epidural analgesia (including history of infectious disease of the central nervous system, history of spinal or intraspinal disease, systemic infection, skin or soft tissue infection at the site of puncture, and coagulopathy).

3.2.5 Other conditions that are considered unsuitable for study participation.

***3.3 Criteria of drop-out***

3.3.1 Exit by participants themselves (i.e., withdraw consents).

3.3.2 Loss to follow-up.

3.3.3 Ordered to exit by the investigators (poor compliance, occurrence of severe complications, or occurrence of severe adverse events).

For drop-out cases, detailed reasons should be recorded. The primary therapeutic effects recorded in the last time will be regarded as the final results. The cases will be included in the intention-to-treat analysis. The Case Report Forms of these cases will be kept for future reference.

***3.4 Criteria of elimination***

Included patients will be excluded if they meet any of the following criteria:

3.4.1 Withdraw consents before intervention.

3.4.2 Do not receive any designated oral beverage.

3.4.3 No assessment result of the primary outcome.

The causes of elimination should be explained. The case will be excluded from the intention-to-treat analysis. The case report forms will be preserved for reference.

***3.5 Criteria of study interruption***

Study will be discontinued if any of the followings happens.

3.5.1 Severe safety problems.

3.5.2 Severe mistake in the protocol.

3.5.3 Support withdrawn by the sponsor or management reasons.

3.5.4 Study cancelled by the administrative department.

Study suspension may be temporary or permanent. In case the study is suspended, all records will be filed for future reference.

**4. Study design**

***4.1 Type of the study***

This is a multicenter, randomized controlled trial with two parallel arms.

***4.2 Sample size calculation***

In a pilot trial of our own, the rate of cesarean delivery was 8% of parturients with carbohydrate drink and 12% of those with clear liquid drink. We assumed similar rates in the present study. With the significance level set at 0.05 (two-sided) and power set at 80%, the sample size required to detect difference was 1760 parturients. Considering a drop-out rate of about 10%, we plan to enroll 2000 parturients. Sample size calculation was performed with the Stata 10.0 software (Stata Corp. LP, College Station, TX, USA).

***4.3 Study center***

This trial will be conducted in 9 obstetric-led maternity units in tertiary hospitals in China. Nine hospitals expected to participate in this study are Peking University First hospital; Woman's Hospital of Nanjing Medical University; Tangshan Maternity and Child Health Care Hospital; Foshan Maternal and Child Health Hospital; Gansu Provincial Maternity and Child Care Hospital; Urumqi Women and Child Health Care Hospital; Linyi people's hospital; Anhui Women and Child Health Care Hospital; Women's Hospital of Zhejiang University.

**5. Randomization and blinding**

***5.1 Randomization principle***

5.1.1 A biostatistician, who is independent of data management and statistical analyses, generates random numbers in a 1:1 ratio with a block size of 4 using the SAS 9.2 software (SAS Institute, Cary, NC). Randomization is stratified according to the study centers.

5.1.2 Study beverages (carbohydrate-rich beverage and commercially available low-carbohydrate beverages) are provided according to the randomization results by an anesthesiologist who does not participate in the other part of the study.

5.1.3 The results of randomization are sealed in opaque, sequentially numbered envelopes and stored at the sites of investigation.

***5.2 Blinding***

Because of the apparent differences in oral drink appearance, study participants, healthcare providers, and investigators are not masked from the study group allocation; however, cesarean delivery rate, maternal sensation of hunger and thirst, and maternal and neonatal blood glucose will be recorded or assessed by outcome assessors who are not involved in perinatal care.

***5.3 Emergency unblinding***

5.3.1 In emergency cases (such as sudden deterioration of parturients’ condition), clinicians and investigators can ask for stopping study intervention.

5.3.2 The reasons leading to interruption of study intervention will be recorded in the case report forms.

**6. Interventional protocol**

***6.1 Epidural labor analgesia management***

6.1.1 As a routine practice, cervical dilatation is assessed at 4-hour intervals after delivery room admission. Epidural labor analgesia is initiated when the cervix was dilated to 1 cm or more.

6.1.2 Before the implement of analgesia, an intravenous line is established with Ringer’s lactate solution (50 ml/h; Na^+^ 130 mmol/L, K^+^ 4 mmol/L, 0.009 kcal/ml).

6.1.3 After confirming the position of the epidural catheter inserted between L2-3 or L3-4 intervertebral space, a 10 ml mixture of 0.1% ropivacaine (AstraZeneca AB, Södertälje, Sweden) plus 0.5 μg/ml sufentanil (EuroCept BV, Ankeveen, Netherlands) is administered as a loading dose; an additional 5 ml mixture is administered 10 minutes later if the numeric rating scale (NRS, an 11-point scale where 0=no pain and 10=the worst pain) of pain remained ≥4.

6.1.4 An intermittent epidural bolus pump (ZZB-II; Jiangsu Aipeng Medical Science and Technology Company Ltd., Nantong, China) is attached 30 minutes later, which is established with 200 ml mixture of 0.07% ropivacaine plus 0.45 μg/ml sufentanil and programmed to deliver 6-ml boluses with a lockout interval of 20 minutes and a background infusion of 4 ml/h. The maximal dose limit is 26 ml/h.

6.1.5 The PCEA pump is stopped at the end of the third stage of labor.

***6.2 Study intervention***

6.2.1 Study intervention will be administered during epidural labor analgesia.

6.2.2 Parturients in the carbohydrate-rich group are provided with an oral carbohydrate-rich solution [Outfast®: 285 mOsm/kg, 14.1% carbohydrate (maltodextrin 100g/L, fructose 23.9g/L, glucose 16.9g/L), Na^+^ 2.0 mmol/L, K^+^ 4.9 mmol/L, 0.58 kcal/ml; Yichang Humanwell Pharmaceutical Co, Ltd, Hubei, China] and are advised to drink as will during labor.

6.2.3 Parturients in the low-carbohydrate group are advised to drink commercially available low-carbohydrate beverages as will (Pocarisweat®: 0.26 kcal/ml, Otsuka Pharmaceutical Co. Ltd, Tokyo, Japan; Gatorade®, 0.24 kcal/ml, PepsiCo, Chicago, IL, USA; or Mizone®: 0.21 kcal/ml, Danone, Guangzhou, Guangdong, China).

6.2.4 All participants have free access to water, but solid foods are not permitted.

6.2.5 Dietary intake prior to labor analgesia and after the third stage of labor are not interfered.

***6.3 Intrapartum care***

6.3.1 In the delivery ward, maternal vital signs are monitoring every 1 to 2 hours but more frequently when necessary. Continuous external fetal heart rate monitoring and/or tocodynamometry are performed as indicated.

6.3.2 Obstetric managements such as oxytocin administration, forceps assistance, and cesarean delivery are decided by the attending obstetricians and midwives. Cesarean delivery is decided according to Chinese guidelines [19].

6.3.3 In case of emergency cesarean delivery, epidural anesthesia is performed through the indwelling epidural catheter or, otherwise, combined spinal-epidural anesthesia is performed. For parturients requiring general anesthesia, a rapid sequence induction with endotracheal intubation is performed. Cricoid pressure is applied continuously from loss of protective airway reflexes until accomplishment of endotracheal intubation and cuff inflation. Antacid prophylaxis and nasogastric tube are not routinely used.

6.3.4 All newborns are observed for 2 hours in the delivery room before being transferred to the postpartum ward.

***6.4 Postpartum care***

The rooming-in policy is the standard of care in all participating centers. Breastfeeding is encouraged whenever possible.

**7. Data collection**

***7.1 Prepartum data***

7.1.1 Demographic data, including gender, date of birth, and body mass index.

7.1.2 Diagnosis and medical history, including duration of gestation, gravidity, prepartum comorbidities, comorbid obstetric disease, medical treatment, history of allergy to food and drugs, and prepartum hemoglobin

7.1.3 Subjective discomfort (degree of hunger and thirst) is assessed using the Numeric Rating Scale (NRS, an 11-point scale where 0 indicated no hunger/thirst and 10 indicated the most severe hunger/thirst) at the initiation of epidural labor analgesia.

7.1.4 Maternal blood glucose level is tested using a blood glucose monitor (Accu-Chek®, Roche, Germany) at the initiation of epidural labor analgesia.

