***7.2 Intrapartum data***

7.2.1 Maternal variables, including oxytocin requirements, artificial membrane rupture, dosage of labor analgesia, duration of labor, episiotomy, mode of delivery, maximal temperature, estimated blood loss, volume of oral intake and volume of intravenous fluid.

7.2.2 Pain severity is assessed using the Numeric Rating Scale (NRS, an 11-point scale where 0 indicated no pain and 10 indicated the most severe pain) before analgesia, at 10 and 30 minutes after analgesia, and at full cervical dilation.

7.3.3 Calculate data, including total fluid intake (oral and intravenous) and calories supplied by oral and intravenous fluid.

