***13.6 Efficacy evaluation***

13.6.1 Primary endpoint:

13.6.1.1 The incidence of cesarean delivery will be calculated. Comparation between groups will be performed using Chi-Square test, with difference between groups expressed as relative risk (95% CI). The upper limit of the 95% CI of less than 1 is regarded as statistical superiority.

13.6.1.2 The interactions between treatment effect and predefined factors will be assessed separately with logistic regression models. The predefined factors include study site, age, body mass index, prepartum anemia, medical comorbidity, obstetric disease, and gynecological disease. The relative risk (and 95% CI) for each subgroup and the P values of treat-by-covariate interactions will be displayed in a forest plot.

13.6.2 Secondary endpoints:

13.6.2.1 Categorial variables (rate of forceps delivery, the rate of neonatal ward admission) between groups will be compared using Chi-Square test, continuity correction Chi-Square test, or Fisher’s exact test. Missing data will not be replaced.

13.6.2.2 Numerical variables (maternal and neonatal blood glucose after giving birth, 1- and 5-minute Apgar scores and the umbilical artery pH value) between groups will be compared using independent sample t-test or Mann-Whitney u test. Missing data will not be replaced.

13.6.2.3 Ranked data (NRS score of hunger/thirst) will be compared using Mann-Whitney u test. Missing data will not be replaced.

13.6.2.4 Relative risk (95% CI) for categorial variables, mean/median difference (95% CI) for numerical variables/ranked data will be calculated.

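### Cervical dilatation at the start of analgesia is not named as a baseline item, and oxytocin and membrane rupture have no time window, so the plan loses a little precision and risks a diluted comparison of co-interventions

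*Protocol*

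**What the plan says.** **Entry point.** Protocol 6.1.1 states that "cervical dilatation is assessed at 4-hour intervals after delivery room admission" and lets the epidural begin at any dilatation from 1 cm upward. Neither that section nor the eligibility criteria in section 3 set an upper limit. Under 6.2.1 the study drink is given during epidural analgesia, so women start it at different stages of labor.

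**Baseline list.** Section 7.1 covers demographics, then "Diagnosis and medical history, including duration of gestation, gravidity, prepartum comorbidities, comorbid obstetric disease, medical treatment" and a few further history items, then hunger, thirst and maternal glucose. The last three are timed to the initiation of analgesia. Dilatation, oxytocin status and membrane status at that moment are not named.

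**Intrapartum list.** Section 7.2.1 begins "Maternal variables, including oxytocin requirements, artificial membrane rupture" and attaches no start time or window to either item. Section 13.5 compares intrapartum variables between groups with simple tests.

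**Analysis.** The primary comparison in 13.6.1.1 is a chi-square test with a relative risk. Section 13.4.2 adds adjustment only for baseline variables whose standardized difference passes a limit. The interaction factors in 13.6.1.2 are "study site, age, body mass index, prepartum anemia, medical comorbidity, obstetric disease, and gynecological disease"; none describes labor status. Randomization (5.1.1) is stratified by center only.

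**The concern.** Dilatation when the drink starts plausibly says how much labor, drinking time and cesarean risk lie ahead. It is known at the bedside, yet the plan does not ask for it as trial data. Three things follow.

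- The balance rule in 13.4.2 cannot detect or adjust for a chance imbalance in a variable that was never collected as baseline.
- Outcome variance that dilatation could explain stays in the primary comparison.
- Oxytocin or membrane rupture that predates the drink cannot be affected by it. If it is counted together with later use, any real difference between arms is pulled toward zero. Care is unmasked (5.2) and the attending team decides on both oxytocin and cesarean delivery (6.3.2), so a reader would look at these comparisons when judging whether the arms were managed alike.

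A later analysis plan could add a covariate or a window, but it could not recover values or start times that were not recorded.

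**Working it through.** **1. The plan's own figure.** Section 4.2 gives the inputs: "the rate of cesarean delivery was 8% of parturients with carbohydrate drink and 12% of those with clear liquid drink" and "With the significance level set at 0.05 (two-sided) and power set at 80"%. With unpooled variance,

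n per arm = (1.960 + 0.842)² × [0.08×0.92 + 0.12×0.88] / 0.04² = 7.849 × 0.1792 / 0.0016 = 879.1, rounded up to 880.

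The total is 1760, which matches "the sample size required to detect difference was 1760 parturients". Allowing for 10% drop-out, 1760/0.9 = 1956, so the planned 2000 is enough. This figure rests on an unadjusted comparison and does not change.

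**2. Power with 900 evaluable per arm** (2000 less 10%). SE = √(0.1792/900) = 0.01411. Noncentrality = 0.04/0.01411 = 2.835. Power = Φ(2.835 − 1.960) = 80.9% (80.8% with the pooled variance under the null).

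**3. Gain from adjusting for dilatation.** The protocol gives no cesarean risk by dilatation, so the gradients are assumptions. With overall risk 10%, R² = var(risk)/(0.10×0.90), and noncentrality is divided by √(1 − R²).

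| Assumed gradient | R² | Power |
| --- | --- | --- |
| None (unadjusted) | 0 | 80.9% |
| Thirds at 16/10/4% | 0.0024/0.09 = 2.7% | Φ(2.873 − 1.960) = 81.9% |
| Thirds at 20/8/2% | 0.0056/0.09 = 6.2% | Φ(2.927 − 1.960) = 83.3% |

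A second set of assumptions spreads dilatation 25/35/25/10/5% over 1 to 5 cm (power from the pooled-variance version, which starts at 80.8%). An odds ratio per cm of 0.9 gives R² 0.1% and power 80.8%; 0.7 gives 1.2% and 81.2%; 0.5 gives 3.7% and 82.2%. Over both sets the gain runs from about 0 to 2.5 points.

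**4. What the balance rule would miss.** The limit in 13.4.2 at 1000 per arm is 1.96 × √(2000/1,000,000) = 0.088. An imbalance of that size shifts the cesarean difference by about √R² × 0.3 × 0.088, where 0.3 = √(0.10×0.90). For R² of 2.7% this is 0.163 × 0.3 × 0.088 = 0.4 points; for 6.2% it is 0.249 × 0.3 × 0.088 = 0.7 points. The planned difference is 4 points.

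**5. Dilution of an ever-use comparison.** Let q be the share already exposed before the drink, equal in both arms. Ever-use = q + (1 − q) × new use, so the risk difference is multiplied by (1 − q). The protocol gives no q. For illustration, take q = 30% and new use of 40% versus 46% among the rest, with 900 per arm:

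| Counting rule | Rates | Difference | SE | z |
| --- | --- | --- | --- | --- |
| Ever-use, all women | 58.0% vs 62.2% | 4.2 points | 0.0231 | 1.82 |
| New use, all women as denominator | 28.0% vs 32.2% | 4.2 points | 0.0216 | 1.94 |
| New use, women not yet exposed (630 per arm) | 40% vs 46% | 6.0 points | 0.0278 | 2.15 |

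The middle row matters for the fix: counting only new use does not restore the difference unless the denominator is also restricted.

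The result depends on q. With the same new-use rates, the ever-use difference is 5.4 points at q = 10%, 4.8 at 20% and 3.6 at 40%. That z passes 1.96 in one row and not in another is an accident of the chosen inputs.

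**The case against.** The strongest case against is that this is an omission of detail, not an error. Several parts of it stand.

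- An unadjusted chi-square test is valid in a randomized trial, and its sample size is reproduced. Chance imbalance in an unlisted covariate is part of the random error that the confidence interval already covers.
- A reader might infer that labor status is not collected, or that use before and after the drink is deliberately pooled. The text does not say so. Sections 7.1.2 and 7.2.1 both present their items as examples, the history items mention medical treatment, and 7.2.1 is silent on timing. What is firm is that these items are not named and no window is given.
- Oxytocin and membrane rupture are neither primary nor secondary outcomes (8.1, 8.2), and the protocol does not assign them the role of a check on differential care. Section 1 holds that calorie supply affects contractions, so a difference in oxytocin use could also be an effect of the drink.
- With examinations four hours apart, the last dilatation may be hours old when analgesia starts. A fresh value could need another examination, so the routine value is the one to ask for.
- The protocol does not say whether allocation precedes the epidural. If it does, oxytocin status at initiation is measured after an open allocation, and using it as a covariate needs care.

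What this does not answer is that 13.4.2 depends on the baseline list, and that data never recorded cannot be restored at analysis.

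**Conclusion.** The point holds as a minor improvement to data collection and analysis. Dilatation governs entry to the intervention but is not named as baseline, so neither the balance rule nor the primary analysis can rely on it. Oxytocin and membrane rupture lack a window, so an ever-use comparison would be diluted by exactly the share already exposed.

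The gain on the primary outcome is small: about 0 to 2.5 power points on a base of roughly 81%, and only if an adjusted analysis is adopted. The risk gradients, the dilatation spread, q and the new-use rates are all assumptions.

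A reader might go further and conclude that the trial is underpowered or its primary result biased. The documents do not support that: "Considering a drop-out rate of about 10%, we plan to enroll 2000 parturients" covers the requirement, and randomization protects against systematic imbalance.

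**What to change.** - **7.1:** at initiation of analgesia, record the last routine cervical dilatation, whether oxytocin was already running, and whether the membranes had already ruptured. No extra examination is needed.
- **13.6.1:** pre-specify dilatation as a covariate in an adjusted relative risk for cesarean delivery. Include prior oxytocin as well, provided it is recorded before allocation; the protocol should state the order of allocation and epidural so that this can be checked.
- **7.2.1:** record whether oxytocin and artificial membrane rupture began after initiation of analgesia.
- **13.5:** compare new use among women not already exposed, since counting new use over all women leaves the difference diluted. The same condition on timing relative to allocation applies to the exposure status that defines this group.

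The cost is three extra baseline fields, a before/after marker on two existing items and slightly more analysis work, for a modest gain in precision.
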